### Exclusion criteria

Use of GERD-related drugs such as acid inhibitors, antacids, prokinetics, gastric mucosal protectors, and herbs (see Additional file 1: Appendix 4) or probiotics and probiotic-related preparations in the last 2 weeks; Any of the following conditions:Liver insufficiency, defined as alanine aminotransferase (ALT) or aspartate aminotransferase (AST) > 2 × the upper limit of normal (ULN);Renal insufficiency, defined as serum creatinine (Scr) > 1 × ULN;Heart failure or electrocardiogram (ECG) abnormalities;Peptic ulcer and bleeding, oesophageal gastric varices, or upper gastrointestinal malignancies confirmed by endoscopy at tertiary hospitals in China in the last 3 months; Myocardial infarction, stroke, or malignant tumour; History of gastro-oesophageal or duodenal surgery; Plans to become pregnant or father a child in the near future, or pregnancy or breastfeeding in women. Inability to cooperate, such as an inability to understand the informed consent form or unwillingness to provide personal information; Allergies to the study drug (rabeprazole) or probiotics; Oesophagitis caused by gastric retention and pyloric obstruction.

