**Method:**

This is a randomized, double-blind, placebo-controlled trial. A total of 120 eligible patients with GERD will be randomized into the experimental group or the control group. The treatment includes two phases: the initial treatment period lasts 8 weeks (weeks 1–8), and the maintenance treatment period lasts 4 weeks (weeks 9–12). During the initial treatment period, the experimental group will take rabeprazole and LiHuo probiotics, and the control group will take rabeprazole and a probiotic placebo; during the maintenance treatment period, the experimental group will take LiHuo probiotics, and the control group will take a probiotic placebo. The primary measure is the change in the GM. The secondary measures are the Reflux Disease Questionnaire (RDQ) score, Gastrointestinal Symptom Rating Scale (GSRS) score, faecal metabolome (FM), body mass index, Los Angeles grade of oesophagitis, adverse event (AE) rate and treatment compliance. Each outcome indicator will be assessed at day 0 (before administration), day 28 and/or 56 (during administration), and day 84 (end of administration) to reveal intragroup differences. AEs will be monitored to assess the safety of LiHuo probiotics.

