Moderate alterations to the upper and distal gut microbiota were observed in patients who used PPIs [8], and changes in the microbiota of the gastrointestinal tract are also associated with PPIs. Previous studies have shown that PPI use results in an increase in multiple taxa from the orders *Lactobacillales* (e.g., *Enterococcaceae* and *Streptococcaceae*) and *Bacillales* (e.g., *Staphylococcaceae*), as well as from the families *Pasteurellaceae* and *Enterobacteriaceae,* and a decrease in the families *Bifidobacteriaceae*, *Ruminococcaceae*, and *Lachnospiraceae* and the class *Mollicutes*. PPIs have the most significant impact on the microbiota in addition to antimicrobials according to the literature [9]. A study indicated that the GM of rheumatoid arthritis (RA) patients who were receiving PPIs was different, as *Streptococcus* was enriched in RA patients who received PPIs. The gut microbiota of PPI users could be modified by the production of virulence factors. This featured microbial function was positively correlated with the relative abundance of *Streptococcus* [10]. Frequent use of PPIs was associated with an increased risk of RA in women, with a higher risk observed in people with a longer PPI treatment period [11]. Researchers of one team observed positive effects of a multispecies probiotic in patients undergoing long-term PPI therapy. The richness of *Stomatobaculum* in the microbiome was decreased and that of *Bacillu*s increased during the intervention, and gastrointestinal quality of life simultaneously showed significant improvements. However, only sparse evidence can support the routine use of probiotics during PPI therapy [12].

In a clinical study on children, the incidence of gut microbial dysbiosis in children treated with PPIs combined with probiotics was only 6.2%, and 56.2% of children who used PPIs and placebo after 12 weeks developed gut microbial dysbiosis. Taking probiotics reduces the incidence of gut microbial dysbiosis in children receiving PPI treatment [13]. Additionally, probiotics can significantly reduce the frequency of reflux, promote gastric emptying, and improve reflux symptoms in infants [14, 15].

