### Volunteer recruitment

Posters will be disseminated at the hospital to recruit participants. During their appointment at the Department of Gastroenterology in the First Affiliated Hospital of Nanchang University, volunteers who are interested in the study will undergo preliminary evaluations based on the inclusion and exclusion criteria. Additionally, the investigator will explain the purpose, process, and potential benefits and risks of this study, and the volunteers may choose to participate by signing the informed consent form. Next, the volunteers will undergo further screening to determine their eligibility. Eligible participants will receive the study intervention and follow-up. The following steps describe the formal intervention and follow-ups (Table 1).

**Table 1 Tab1:** Study and follow-up schedule

Item^1,10^		Screening	Baseline	Initial treatment		Maintenance treatment
		Visit 0	Visit 1	Visit 2	Visit 3	Visit 4
		Days −3 to 0	Day 0	Week 4	Week 8	Week 12
Basic demographics		X				
Vital signs, physical examination		X				
Allergies, medical history^2^, medication history^3^, surgical history^4^		X				
Smoking and drinking		X				
Gastroscopy		X^5^				X^6^
Abdominal ultrasound B^7^		X				
Serum human chorionic gonadotropin (hCG)		X				
ECG		X				X
Blood test, urine analysis, stool test (including occult blood)		X				X
Liver/kidney function^8^		X				X
Signed informed consent		X				
Inclusion/exclusion criteria verification			X			
Primary outcome measure	GM^11^ (metagenomics)	X		X	X	X
Secondary outcome measures	RDQ	X	X	X	X	X
	GSRS		X	X	X	X
	Faecal metabolomics^11^	X		X	X	X
	BMI ^9^		X	X	X	X
	LA grade	X				X
Safety measures	AEs			X	X	X
	SAEs			X	X	X
Compliance verification			X	X	X	
Concomitant medications		X	X	X	X	

^1^Visit window: 0 days for visit 1; ± 2 days for visits 2, 3, and 4

^2^Medical history: current and past illnesses, including peptic ulcer, gastritis, oesophagitis, cardiovascular and cerebrovascular diseases, cancer, and mental illness

^3^Medication history: PPI, histamine H2 antagonists, antibiotics, probiotics, prokinetics, gastric mucosal protectors, and other drugs for gastro-oesophageal reflux (including herbs)

^4^Surgical history: gastrointestinal surgeries, including gastro-oesophageal and duodenal surgeries

^5^Performance of gastroscopy in domestic tertiary or higher hospitals in the past 3 months

^6^Gastroscopy at visit 4, LA grades at visit 0 and visit 4 referring to patients with oesophagitis (LA-A, LA-B or LA-C)

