### Intervention strength and management

Rabeprazole: 10 mg/tablet, from Eisai China, Inc (Tokyo, Japan).

LiHuo Probiotics powder: LiHuo probiotics powder containing strains such as *Lactobacillus casei Zhang*, *Bifidobacterium lactis* V9, and *Lactobacillus plantarum* P9, 2 g/bar, each bar containing active probiotics (≥ 50 billion CFU), were obtained from Jiangzhong Pharmaceutical Company Limited (China). During the manufacturing of LiHuo probiotics powder, *Lactobacillus casei Zhang*, *Bifidobacterium lactis* V9, and *Lactobacillus plantarum* P9 were mixed according to concentrations of ≥ 5 billion CFU/g, ≥ 15 billion CFU/g, and ≥ 5 billion CFU/g, respectively.

Probiotic placebo powder: The ingredients are maltodextrin, orange powder, and maltitol, and there are no active ingredients. The appearance, packaging, storage method, and dosing are the same as those of the LiHuo probiotics from Jiangzhong Pharmaceutical Company Limited (China).

The rabeprazole, LiHuo probiotics, and probiotic placebo will be stored in a cool, dry place away from light. Refrigerated storage will retain the maximum activity of the product. Each patient will receive a sample that corresponds to his or her unique number. All remaining study drugs and empty packages will be collected at the end of the study.

The study will have three phases: the screening period, the initial treatment period, and the maintenance treatment period. The interventions in each phase are described below:Screening: No intervention.Initial treatment (weeks 1–8):Control group: rabeprazole and probiotic placebo. The samples will be distributed to the patients every month.Experimental group: rabeprazole and probiotics. The samples will be distributed to the patients every month.Rabeprazole dosage: 10 mg/tablet twice a day before meals;Dosage of probiotic placebo or LiHuo probiotics: 2 bars, once a day, with or without water (< 40 °C), after meals. Thus, the daily dosage of probiotics is more than 100 billion CUF. Participants who take antibiotics should wait 2 h before taking the probiotic placebo or LiHuo probiotics.Maintenance treatment (weeks 9–12):

Control group: probiotic placebo. The samples will be distributed to the patients every month.

Experimental group: probiotics. The samples will be distributed to the patients every month.

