### To minimize confounding interventions

 Prohibited treatments during the study. Probiotics, prebiotics, and foods containing probiotics (such as yogurt) other than those used in this study; Drugs for gastro-oesophageal reflux, such as acid inhibitors, antacids, gastric mucosal protectors, prokinetics, and equivalent drugs [19, 20] (see Additional file 1: Appendix 4) other than the study drug; Antibiotics and probiotics should be taken 2 h apart; Participants will be instructed to avoid spicy foods and to abstain from smoking or drinking during the study.

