### Statistical analysis

First, the intention-to-treat (ITT) analysis will be conducted between the two groups, including all the intended participants who do or do not complete the follow-up. Then, per-protocol (PP) analysis will be conducted in the four-subgroup datasets according to compliance (100%, ≥ 80%, 60–80%, and < 60%) to validate the robustness of the results. The datasets will be analysed as described below.

With a randomized block design, the nonparametric rank sum test and Friedman M test will be performed to analyse the difference in each outcome measure at each time point (see “Intervention Outcome Measures” for details) between the two groups, including the GM analysis, RDQ score, GSRS score, faecal metabolomics, and BMI. The significance level will be set to *P* = 0.05. Next, the paired Wilcoxon signed-rank test will be performed for pairwise intragroup comparisons to analyse the change trends for each outcome measure before, during, and after the probiotic intervention. The significance level will be set at *P* = 0.05/[k(k-1)/2], where k is the number of groups in the comparison. For analysis of the oesophagitis grade, the diagnosis of LA-B at baseline and LA-A at week 12 indicates that the patient's oesophagitis grade will have decreased by one level. If the grade is LA-C at baseline and LA-A at 12 weeks, the patient’s oesophagitis grade will have decreased by 2 levels. The number of oesophagitis grades reduced by 1 and 2 levels in each group will be calculated. Then, a chi-square (*χ*^2^) test will be performed. AE rates in the two groups will be compared by the *χ*^2^ test or Fisher’s exact probability test based on the occurrence frequency of AE, and the difference in treatment compliance will be also examined by the *χ*^2^ test.

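### The entry exclusion does not name the probiotic foods that are banned on study, so within-arm changes from baseline may mix dietary withdrawal with treatment effect

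*Protocol article*

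**What the plan says.** The protocol article treats outside sources of probiotics in two places.

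- *Exclusion criteria*: recent use of listed GERD drugs "or probiotics and probiotic-related preparations in the last 2 weeks" rules a patient out. Foods are not mentioned, and prebiotics are not named.
- *To minimize confounding interventions*: under "Prohibited treatments during the study" the list reads "Probiotics, prebiotics, and foods containing probiotics (such as yogurt) other than those used in this study".

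The timing comes from three places. Table 1 marks the first gut-microbiome (GM) sample at Visit 0 (Days −3 to 0) and marks none at Visit 1; *Primary outcome* calls this sample day 0. *Intervention strength and management* says of the first phase "Screening: No intervention", and no dietary lead-in is described. The history taken at screening is "Medication history: PPI, histamine H2 antagonists, antibiotics, probiotics, prokinetics, gastric mucosal protectors" and other reflux drugs. It includes probiotics, but not prebiotics or probiotic foods, and Table 1 has no row for diet.

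On analysis, the abstract says that outcomes are assessed over time "to reveal intragroup differences". *Statistical analysis* plans rank-based tests between the two groups at each time point, after which "the paired Wilcoxon signed-rank test will be performed for pairwise intragroup comparisons". *Sample size* rests on the between-group difference at week 12.

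**The concern.** By placing foods containing probiotics under a heading about confounding, the protocol itself treats them as able to disturb the primary outcome. It lists them separately from probiotics, so an entry clause about preparations does not naturally reach them. A daily yogurt eater is eligible as the text stands. That patient can give the baseline stool while exposed and must then stop at about the time rabeprazole and the study powder begin. Baseline and weeks 4, 8 and 12 are then sampled under different dietary conditions.

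What is at stake is the reading of change from baseline within each arm. In affected patients that change contains withdrawal of the food as well as whatever the assigned treatment does. As the article describes data collection, nothing would identify these patients afterwards, so the analysis could not separate the two.

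**Working it through.** **1. The two lists side by side**

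| Exposure | Entry, last 2 weeks | During the study |
|---|---|---|
| Probiotic products | excluded | prohibited |
| Prebiotics | not named; may or may not fall under probiotic-related preparations | prohibited |
| Foods containing probiotics | not named | prohibited |

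The food row is a clear gap. The prebiotic row is an ambiguity.

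**2. The plan's own sample size.** Inputs from *Sample size*: Chao1 difference 145, SD 230, α = 0.025, power 0.80.

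n per group = 2 × [230 × (z(0.9875) + z(0.80)) / 145]² = 47.83

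This agrees with the stated 47.9 if α is taken as two-sided. Then 47.9 × 1.2 = 57.5, as stated. Power is 0.80 at 48 per group and 0.89 at 60. None of these figures depends on the eligibility wording.

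**3. Sensitivity, on assumed values.** Let f be the share of each arm who are users at baseline and D the Chao1 shift on stopping. The documents give neither. The ranges used are f = 0.1–0.5 and D = 50–145, the upper end of D being the planned treatment difference.

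- Shift in the within-arm mean change = f × D
- Expected between-arm bias, if D is the same in both arms = f × D − f × D = 0
- SD of the between-arm difference from chance imbalance in users, 48 per arm = D × √[2f(1 − f)/48]
- Inflated outcome SD = √[230² + f(1 − f)D²], then power at 48 per arm

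| f | D | Within-arm shift | SD from chance imbalance | Inflated SD | Power |
|---|---|---|---|---|---|
| 0.1 | 50 | 5 | 3.1 | 230.5 | 0.80 |
| 0.2 | 100 | 20 | 8.2 | 233.5 | 0.79 |
| 0.3 | 145 | 43.5 | 13.6 | 239.4 | 0.77 |
| 0.5 | 145 | 72.5 | 14.8 | 241.2 | 0.76 |

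**4. Could the shift alone give a significant paired test?** Four time points give k(k − 1)/2 = 6 pairs, so the plan's level is 0.05/6 = 0.0083. Assume an SD of change of 230 (a within-patient correlation of 0.5) and 48 patients, and use a normal approximation in place of the signed-rank test. The probability of significance in the direction of the shift is Φ[fD/(230/√48) − z], with z for two-sided 0.0083. It is 0.006 at a shift of 5 and 0.325 at a shift of 72.5. With no shift it would be 0.0083/2 = 0.004.

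**The case against.** The strongest reply is that the comparison on which the trial is sized is safe. Arms are randomized and blinded, and both face the same ban, so a common withdrawal shift cancels. Even if the study powder replaces the withdrawn food in one arm only, the contrast is still a valid randomized effect, though in a partly withdrawn population. This stands, and it limits the point to within-arm change.

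Other parts of the reply also stand:

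- The term for probiotic-related preparations is undefined and may cover prebiotics, and the appendices are not shown.
- The ban runs during the study, and screening is described as one of its phases. It may therefore start up to about 3 days before dosing, so exact coincidence with the first rabeprazole dose is not documented.
- Participants are also told to avoid spicy food, smoking and drinking, with no lead-in. Aligning the probiotic lists would not make baseline and follow-up conditions identical.

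A reader might infer that a placebo-arm fall in *Bifidobacteriaceae* will be reported as a rabeprazole effect, since *Background* links PPI use to an increase in some taxa "and a decrease in the families" that include it. The documents do not support this. Nowhere do they say that placebo-arm change will be attributed to rabeprazole, and they do not say which organisms the withdrawn foods supply. *Background* also reports PPI-related increases in *Lactobacillales*; stopping a food rich in lactobacilli would push that order the other way. A loss of precision in a baseline-adjusted comparison might also be inferred, but the article states no such comparison.

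None of this removes the mismatch, or the missing record of who was exposed at baseline.

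**Conclusion.** The point holds in a limited form. The entry exclusion and the on-study ban do not match for foods containing probiotics, and their match for prebiotics is unclear. A supplemented baseline followed by unsupplemented follow-up is therefore possible, and the planned paired within-arm changes from baseline may mix dietary withdrawal with treatment effect.

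The size is unknown. Under the assumed ranges the within-arm mean change is off by 5 to 72.5 Chao1 units, against a planned between-group difference of 145. The upper figure needs half of each arm to be users and a shift as large as the whole planned effect.

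A reader might conclude that the primary between-group result is biased. It is not, in expectation: the cost there is some noise, with power at 48 per arm going from 0.80 to 0.76 at the extreme. This is a cheap improvement to the interpretation of a supporting analysis and no threat to the week-12 comparison.

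**What to change.** Reconcile *Exclusion criteria* with *To minimize confounding interventions*, so that one list of probiotics, prebiotics and foods containing probiotics applies before the Visit 0 stool as well as during the study. The length of the window is for the investigators to set. A patient ruled out only on this ground should be allowed to re-screen.

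At minimum:

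- add recent prebiotic and probiotic-food intake to the Visit 0 history;
- repeat the within-arm tests without recent users;
- do not attribute within-arm change to rabeprazole or the study product alone.

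The full fix costs one eligibility clause and one screening question. Some patients would also start later, and those deferred may need new blood, urine, stool and liver/kidney tests, because Table 1 accepts such results only from the past week. How many would be deferred cannot be said, since the documents give no prevalence; at the assumed 10–50% it would be 12 to 60 of 120. The minimum version defers nobody.

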### Randomization and blinding

According to their order of participation in the study, volunteers who sign the informed consent form will be assigned a screening number (e.g., 010,001, 010,002, 010,003, 010,004, 010,005); then, they will receive a serially unique number (e.g., G1001, G1002, G1003, G1004, G1005) according to their screening result. For each of these unique numbers, a random sequence will be generated by the computer software R 4.1.0 and used to randomly assign the unique number (representing a volunteer) to the probiotic group or placebo group. During the study, the subjects and study staff responsible for sample distribution, data collection, data collation and analysis will be blinded to the random sequence, which will be maintained by two independent project managers and unblinded only in the case of important safety issues, and the final data analysis will be completed. Moreover, an independent project administrator will label the probiotics or placebo packs with unique numbers corresponding to random sequences in advance to achieve allocation concealment. According to the order of randomization, the distributor will distribute the treatment packs to the corresponding volunteers.

### Study intervention

The study treatment consists of two phases: an initial treatment period lasting 8 weeks (weeks 1–8) and a maintenance treatment period lasting 4 weeks (weeks 9–12). The patients will be randomized into two groups: a control group and an experimental group. The participants will not know the group to which they have been assigned.

### Intervention strength and management

Rabeprazole: 10 mg/tablet, from Eisai China, Inc (Tokyo, Japan).

LiHuo Probiotics powder: LiHuo probiotics powder containing strains such as *Lactobacillus casei Zhang*, *Bifidobacterium lactis* V9, and *Lactobacillus plantarum* P9, 2 g/bar, each bar containing active probiotics (≥ 50 billion CFU), were obtained from Jiangzhong Pharmaceutical Company Limited (China). During the manufacturing of LiHuo probiotics powder, *Lactobacillus casei Zhang*, *Bifidobacterium lactis* V9, and *Lactobacillus plantarum* P9 were mixed according to concentrations of ≥ 5 billion CFU/g, ≥ 15 billion CFU/g, and ≥ 5 billion CFU/g, respectively.

Probiotic placebo powder: The ingredients are maltodextrin, orange powder, and maltitol, and there are no active ingredients. The appearance, packaging, storage method, and dosing are the same as those of the LiHuo probiotics from Jiangzhong Pharmaceutical Company Limited (China).

The rabeprazole, LiHuo probiotics, and probiotic placebo will be stored in a cool, dry place away from light. Refrigerated storage will retain the maximum activity of the product. Each patient will receive a sample that corresponds to his or her unique number. All remaining study drugs and empty packages will be collected at the end of the study.

The study will have three phases: the screening period, the initial treatment period, and the maintenance treatment period. The interventions in each phase are described below:Screening: No intervention.Initial treatment (weeks 1–8):Control group: rabeprazole and probiotic placebo. The samples will be distributed to the patients every month.Experimental group: rabeprazole and probiotics. The samples will be distributed to the patients every month.Rabeprazole dosage: 10 mg/tablet twice a day before meals;Dosage of probiotic placebo or LiHuo probiotics: 2 bars, once a day, with or without water (< 40 °C), after meals. Thus, the daily dosage of probiotics is more than 100 billion CUF. Participants who take antibiotics should wait 2 h before taking the probiotic placebo or LiHuo probiotics.Maintenance treatment (weeks 9–12):

Control group: probiotic placebo. The samples will be distributed to the patients every month.

Experimental group: probiotics. The samples will be distributed to the patients every month.

Dosage of probiotic placebo or LiHuo probiotics: 2 bars, once a day, with or without water (< 40 °C), after meals. Participants who take antibiotics should wait 2 h before taking the probiotic placebo or LiHuo probiotics.

